## Abstract

**Background:**

Compared to healthy controls, cancer patients have a higher risk of unemployment, which has negative social and economic impacts on the patients and on society at large. Therefore, return-to-work of cancer patients needs to be improved by way of an intervention. The objective is to describe the development and content of a work-directed intervention to enhance return-to-work in cancer patients and to explain the study design used for evaluating the effectiveness of the intervention.

**Development and content of the intervention:**

The work-directed intervention has been developed based on a systematic literature review of work-directed interventions for cancer patients, factors reported by cancer survivors as helping or hindering their return-to-work, focus group and interview data for cancer patients, health care professionals, and supervisors, and vocational rehabilitation literature. The work-directed intervention consists of: 1) 4 meetings with a nurse at the treating hospital department to start early vocational rehabilitation, 2) 1 meeting with the participant, occupational physician, and supervisor to make a return-to-work plan, and 3) letters from the treating physician to the occupational physician to enhance communication.

**Study design to evaluate the intervention:**

The treating physician or nurse recruits patients before the start of initial treatment. Patients are eligible when they have a primary diagnosis of cancer, will be treated with curative intent, are employed at the time of diagnosis, are on sick leave, and are between 18 and 60 years old. After the patients have given informed consent and have filled out a baseline questionnaire, they are randomised to either the control group or to the intervention group and receive either care as usual or the work-directed intervention, respectively. Primary outcomes are return-to-work and quality of life. The feasibility of the intervention and direct and indirect costs will be determined. Outcomes will be assessed by a questionnaire at baseline and at 6, 12, 18, and 24 months after baseline.

**Discussion:**

This study will provide information about the effectiveness of a work-directed intervention for cancer patients. The intention is to implement the intervention in normal care if it has been shown effective.

**Trial registration:**

NTR1658

## Background

Since the survival rates of cancer have increased considerably in recent years, the long-term side effects of cancer and cancer-related treatments may impact survivors' capabilities to regain normal lives. This implies that some forms of cancer are becoming chronic diseases entailing both poorer overall quality of life compared to the general population and disabling long-term residual symptoms, such as fatigue, depression, pain, and functional limitations [1-3]. One aspect of regaining a normal life after cancer is returning to work, which is often seen by cancer survivors as an important part of recovery [4-6]. Furthermore, the loss of work of cancer survivors is associated with lower quality of life, lower self-esteem, and worse financial situations [7,8]. Unfortunately, not all cancer survivors return-to-work. A meta-analysis showed that the risk of unemployment is 37% higher for cancer survivors compared to healthy controls [9]; cancer survivors also experience work limitations [10,11]. The employer and society at large are also affected due to absenteeism, disability pensions, and loss of productivity [12]. Furthermore, cancer survivors get little advice from their treating physicians about return-to-work issues, and they experience a lack of guidance from their general practitioners or occupational physicians as well [13,14]. Considering these negative work-related side effects for cancer survivors and the lack of attention toward these problems, there is ample room to improve return-to-work with an appropriate intervention.

A systematic review of the literature [15] concerning work-directed interventions for cancer patients showed that well-developed work-directed interventions are limited and that the methodological quality of these studies is moderate. This indicates that a new intervention needs to be developed and that its effectiveness on return-to-work and quality of life should be determined by a randomised controlled trial. Considering the financial impacts on cancer patients and society at large, the direct and indirect costs should also be taken into account.

Return-to-work is only one aspect of survivor care and it should not be dealt with in isolation. Therefore, we developed the intervention in such a way that it fits the shared-care model for cancer survivor care [16]. This model encompasses a work-directed intervention integrated into cancer care as integrated into the occupational physician or general practitioner's care, establishing active communication between these health care professionals.

### Objective

The objective is to describe the development and content of a work-directed intervention to enhance return-to-work in cancer patients and to explain the study design used for evaluating the effectiveness of the intervention.

## Development of the intervention

The development of the work-directed intervention is based on the following: 1) a systematic review concerning the content of work-directed interventions for cancer patients, 2) factors reported by cancer survivors as helping or hindering their return-to-work, 3) focus group data of cancer survivors and of supervisors regarding return-to-work after cancer, 4) vocational rehabilitation literature, and 5) semi-structured interviews with health care professionals.

First, the systematic review described the content of work-directed interventions for cancer patients on the basis of the two most important prognostic factors for return-to-work that can be directly altered by a work-directed intervention: self-perceived work ability and physical workload [5,17]. Of the 19 included studies, 18 addressed work ability and 6 addressed physical workload. The following interventions to address work ability proved to be suitable: making a return-to-work plan, individual counselling/structural guidance, and cognitive behavioural therapy, and provision of an educational leaflet. The interventions that were shown to be suitable to address physical workload were: workplace accommodations and occupational or vocational training.

Second, we incorporated factors reported by cancer survivors as helping or hindering their return-to-work. These factors were measured in a prospective cohort study of Spelten et al. [18] with two-open questions: "*what or whom helped you the most with regard to work resumption or continuing work?" *and *"what or whom hindered you the most with regard to work resumption and continuing work" *[18]. Cancer survivors answered these open-ended questions at 6, 12, and 18 months after their first day of sick leave. We used the International Classification of Functioning (ICF) as a theoretical framework to categorise the answers into factors underlying work-related disability: body structure and functioning, environment-related factors, and person-related factors [19,20]. The most frequently reported factor that aided in return-to-work in the category of body structure and functioning was general health; the most frequently reported hindering factor was fatigue. With regard to environment-related factors, managers, colleagues, and family were the most frequently reported helping factors and workload a hindering factor. For person-related factors, personality was the most frequently reported helping factor, and distrust in the manager was a hindering factor.

Third, the experiences of cancer survivors and supervisors regarding return-to-work after cancer were assessed in three focus groups [14]. A total of 7 cancer survivors and 6 supervisors participated in the focus groups. The following themes were reported by cancer survivors as being the most important: 1) contact with and support from colleagues and supervisors, 2) the occupational physician's and other physician's advice and expertise, and 3) knowledge of the long-term consequences of cancer, such as fatigue and cognitive problems. The following themes were reported by supervisors as being the most important: 1) their own role and that of the occupational physician, 2) return-to-work aspects such as work accommodations, and 3) communication with all stakeholders. The main findings of these focus groups were that support from colleagues and supervisors aids in return-to-work. Lack of knowledge and advice from occupational physicians and lack of communication between all stakeholders hinders return-to-work [14].

Fourth, because the occupational physician is legalised to advise about the return-to-work of sick-listed employees in the Netherlands, he or she should be part of the intervention. In addition, employer participation is essential for preventing impediments. For instance, for the implementation of workplace accommodations, it is important that the employee, employer, and occupational physician agree. Furthermore, the intervention should be carried out close to the workplace and in collaboration with all stakeholders [21].

Fifth, semi-structured interviews with a radiotherapist and four oncology nurses from four different departments in the Netherlands were held to determine the best way to integrate the intervention into usual cancer care. The health care professionals stated that the intervention should be integrated into psycho-oncological care. This seemed to be feasible based on the results of our systematic review [15].  The interviewees' nurses stated that they lack the knowledge to provide this kind of care but that a training course would help to provide this knowledge. Furthermore, the interviewed nurses and radiotherapist believed that the intervention should be carried out individually because of variations in treatment, survival, and importance of work. In addition, the different factors reported by cancer survivors as helping or hindering their return-to-work also confirm the need to provide individual interventions. The interviewees stated that the psycho-oncological care of cancer patients varies enormously between hospital departments with respect to content, length, duration, extensiveness, and provider. These differences also hold for return-to-work, which is not addressed structurally by any of the departments. However, the interviewees believed that cancer patients need structural guidance in their return-to-work process. To achieve this guidance, they advised that meetings need to be scheduled and that communication with the occupational physician should be improved.

## Content of the intervention

Incorporation of the findings described above resulted in a work-directed intervention that encompasses: 1) 4 meetings of 15 minutes each will be held at the hospital as part of the normal consulting hour to start early vocational rehabilitation. These meetings will be carried out as part of normal psycho-oncological care by an oncology nurse, social worker or nurse practitioner. In this article, we will refer to these people as the nurse. Since usual care differs between hospital departments, the organisation of these meetings may vary slightly, 2) one meeting with the participant, the occupational physician, and the supervisor will be held to make a return-to-work plan, and 3) three letters will be send to the occupational physician to enhance communication; two will be from the treating physician and one from the nurse.

### 1) Meetings at the hospital

The aim of the first meeting is to make a list of potential problems concerning return-to-work and to plan the intervention that best suits the individual participant. The first meeting will take place a few weeks after diagnosis, and the nurse will begin by taking a short work-anamnesis. Thereafter, the nurse will give guidance regarding the best way to inform colleagues and supervisors about the participant's illness and to keep them informed during treatment/aftercare. Furthermore, the participant will receive an informational leaflet about cancer [22]. An educational leaflet that consists of 10 steps of advice [23] will be given to the participant and will be used as a guideline for the intervention. Scheduling of the second meeting will depend on the diagnosis, treatment, and preference of the participant; it will be scheduled for a maximum of 10 months after the first meeting. The aim is to schedule this meeting two months before the participant is expected to return-to-work. This would largely occur at the end of medical treatment, because most cancer patients return-to-work thereafter [18]. However, if a participant wants to return-to-work during treatment, the second meeting will be scheduled two months before the return-to-work is expected.

The second meeting starts with a recapitulation of the topics discussed at the first meeting. Then, barriers to return-to-work will be identified, and actions to remove these barriers will be discussed. This information will be sent to the occupational physician. The identification of barriers to return-to-work and actions to remove these barriers are based on the work-anamnesis, physical, and psychosocial restrictions, coping, individual importance of work, participant preference regarding the return-to-work, and the most important prognostic factors for returning to work, such as, older age, lower education, and blue collar work.

The aim of the third and fourth meetings is to evaluate the process of return-to-work. The third meeting will be scheduled for a maximum of 2 months after the second meeting because during the actual return-to-work, different problems might arise. The barriers to return-to-work and actions to remove these barriers that were discussed in the second meeting will be evaluated. If a return-to-work plan has been made, it will be discussed. If necessary, the return-to-work plan will be altered, and extra information or advice will be provided. Possible medical or psychosocial problems will be discussed, and the patient can be referred to another professional (e.g. a psychologist) if needed. There are two options for the fourth meeting depending on whether the participant has returned to work or not. If a participant has returned to work, the fourth meeting will be scheduled approximately 1 month after the return-to-work, and advice regarding continued employment will be provided. If the participant has not returned to work, the fourth meeting will take place a maximum of 14 months after baseline, and the contents of the third meeting will be discussed.

### 2) Meeting with participant's occupational physician and supervisor

The occupational physicians will be asked to schedule a meeting with the participant, the participant's supervisor, and with himself/herself to make a return-to-work plan. Medical information from the hospital regarding disease, treatment, and long-term side effects as the identified barriers to return-to-work and actions to remove these barriers that were discussed with the nurse can be used as a basis for this discussion. This meeting should be scheduled between the second and third meeting with the nurse, which would be between the second and tenth month after the first day of sick leave. The researcher will request this meeting; the request will be attached to the first letter from the treating physician to the occupational physician. A return-to-work plan will contain the following information: first day of work resumption, the number of hours the participant will work, the task(s) he/she is going to perform, and with which steps patients will increase working hours, working days and/or will do additional or different tasks.

### 3) Enhancing communication between treating physician and occupational physician

In the Netherlands, patients must give their consent to allow medical information to be sent from a treating physician to an occupational physician. A nurse will ask for this consent from each participant during the first meeting. If the participant gives consent, a copy of a letter from their treating physician to their primary care physician (containing general medical information such as diagnosis, prognosis, treatment plan, and outcome treatment) will be sent to their occupational physician. General information about the study (including the educational leaflet) will be attached to this letter. The identified barriers to return-to-work and actions to remove these barriers that were discussed with a nurse will be sent by a nurse to an occupational physician.

## Study design to evaluate the intervention

For the description of the design of our evaluation study, we used the items of the CONSORT statement for improving the quality of reporting randomised trials [24].

### Organisation study

The study is designed as a randomised controlled trial with a follow-up of 2 years. Cancer patients are asked to participate at the hospital. The medical ethics committee of the institution, the Academic Medical Center, approved the study, and the local medical ethics committees of various participating hospitals advised positively about the local feasibility of the study. Patients will sign informed consent forms before participating in the study.

### Recruitment of study population

The treating physician or nurse will inform the cancer patients about the study when they visit the hospital to discuss their treatment plans. The treating physician will check each patient's eligibility by assessing the inclusion and exclusion criteria and provide written information about the study. Then, the researcher will contact the patient by telephone to provide additional information and schedule a meeting with the patient following a visit to the hospital or at the patient's home. After the patient has signed informed consent and filled out a baseline questionnaire, he or she will be randomised to either the control group or the intervention group.

### Participants

Patients are eligible to participate when they have a primary diagnosis of cancer, will be treated with curative intent, are employed at the time of diagnosis, are sick-listed, and are between 18 and 60 years old. Treatment with curative intent was defined as a 1 year survival rate of approximately 80%. The exclusion criteria are: 1) patients who are not able to speak, read or write Dutch sufficiently well, 2) patients who have a severe mental disorder or other severe co-morbidity, 3) Primary diagnosis of cancer has been made more than two months ago, 4) patients who will receive primary treatment at another hospital, and 4) patients who have a primary diagnosis of testicular cancer, non-melanoma skin cancer or melanoma skin cancer. This last exclusion criterion has been selected because, on average, these cancer patients do not experience significant problems with return-to-work; therefore, the intervention would not be useful for the majority of this patient group [5,25].

### Randomisation, blinding and treatment allocation

The researcher will carry out randomisation using the computerised randomisation program ALEA [26]. Allocation of each patient is definite in such a way that allocation concealment is not possible. Because, patients differ significantly between the participating hospital departments in diagnosis and demographic factors, and because these aspects, as well as age, are important prognostic factors for return-to-work, [18] randomisation is stratified by the treating hospital department and age to prevent bias due to unequal randomisation. The cut-off age for stratification is 50. To equalise group sizes, minimisation is applied. If a treating hospital department has more than one nurse, participants in the intervention group will only be seen by nurses who carry out the intervention and vice versa. Participants, nurses, and researchers are not blinded to group assignment. Because all follow-up questionnaires will be filled out at home, no direct influence by the researchers is likely to occur.

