### Methodological considerations of the study design

We used the items of the CONSORT statement for improving the quality of reporting randomised trials as guidance for the study protocol [24]. One drawback of our study design is that in departments with one nurse, the nurse might also give better guidance to participants in the control group leading to contamination. One way to prevent this kind of contamination is to randomise on the hospital department level, so-called cluster randomisation. In our case this had the following disadvantages. Cluster randomisation on the department level will irrevocably lead to baseline differences in patient characteristics, such as diagnosis, treatment, and age because departments deal with specific cancer patients. These baseline characteristics are the most important prognostic factors for return-to-work [17,18] and differ significantly between hospital departments in the Netherlands. Although it is possible to correct for these baseline differences afterward, bias will always be apparent. Further, nurses might invite a specific group of patients to participate in the study since they know in which group each patient will come [44]. At last, psycho-oncology care differs between hospital departments; thus, the outcome might be biased by these differences in usual care. The drawback of our approach is of course contamination. To reduce the likelihood of contamination, nurses must fill out a process form for each patient in each meeting.

We choose not to perform a comprehensive cost effectiveness evaluation in which all direct and indirect costs, such as medical consumption are taken into account because the expectation is that the intervention has no effect on these costs. Therefore, the expectation is that these medical costs are equally divided between groups and therefore do not contribute to the cost analysis. In addition, the aim of our work-directed intervention is to improve participants' return-to-work and work productivity and to reduce absenteeism and lost earnings. Therefore, we choose to perform the economic evaluation on the basis of these work-related costs.

This study will provide information about the effectiveness of our work-directed intervention on return-to-work and quality of life. The results will be available in 2011. Furthermore, the intention is to implement the intervention in normal care if it has been shown effective.

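### The protocol article wrongly says allocation concealment is impossible, although its own sequence (consent, baseline questionnaire, then computerised randomisation) allows it; the sentence gives up a basic safeguard and should be replaced

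*Protocol article*

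**What the plan says.** The section on randomisation, blinding and treatment allocation makes these statements:

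- Who and how: "The researcher will carry out randomisation using the computerised randomisation program ALEA".
- Concealment: "Allocation of each patient is definite in such a way that allocation concealment is not possible".
- Factors: "randomisation is stratified by the treating hospital department and age to prevent bias due to unequal randomisation", and "The cut-off age for stratification is 50".
- Method: "To equalise group sizes, minimisation is applied".
- Blinding: "Participants, nurses, and researchers are not blinded to group assignment".

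The recruitment section gives the order of events. The treating physician or nurse raises the study, and the physician checks eligibility and hands over written information. Then "the researcher will contact the patient by telephone to provide additional information and schedule a meeting". Randomisation comes after the patient has signed consent and completed the baseline questionnaire; the abstract gives the same order. Neither place says who takes consent.

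The methodological considerations reject cluster randomisation for several reasons. One is that "nurses might invite a specific group of patients to participate in the study since they know in which group each patient will come".

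**The concern.** Concealment means that nobody involved in enrolment can know the next allocation before the patient is irrevocably entered. It is separate from blinding, which concerns what is known afterwards. The article says in a sentence of its own that nobody is blinded, so the concealment sentence reads as a further statement and not as a repetition.

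The sentence is a positive statement that a safeguard is absent. It therefore cannot be excused as a detail that a condensed article leaves to the full protocol.

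If it is meant literally, someone who can foresee the arm could press, delay or discourage a patient according to how likely that patient seems to return to work. Several features of the trial would make this hard to repair later:

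- Return-to-work is self-reported and the trial is open-label.
- Prognostic factors enter the effect analysis only if the groups turn out to be imbalanced, and such adjustment cannot remove selection on things that were not measured.
- The one reassurance offered, that follow-up questionnaires are completed at home, concerns outcome reporting and not enrolment.

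**Working it through.** The plan gives no figure on this point. The check is therefore a comparison of passages, followed by an illustration of how predictable allocation could be.

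**1. Is concealment impossible under the described procedure?**

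| Element | Where stated | Effect on concealment |
|---|---|---|
| Randomisation follows consent and baseline | Abstract; recruitment section | Allows it: the arm need not exist before the patient is committed |
| Computer program generates the allocation | Randomisation section | Allows it |
| Allocation is definite | Randomisation section | Supports it: an allocation that cannot be changed cannot be undone once seen |
| No blinding | Randomisation section | Does not decide it: concerns knowledge after allocation |

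None of these makes concealment impossible. The reason given for the impossibility does not lead to it.

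**2. Does the sentence fit the rest of the article?** The case against cluster randomisation relies partly on recruiters knowing the coming group. A design that disclaims concealment cannot claim a clear advantage on that count. The risks are related but not identical. Under cluster allocation nurses know the group with certainty; here nurses do not randomise, and nothing says they see any totals.

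**3. Who could act on foreknowledge?** An unblinded researcher telephones patients and arranges to meet them before consent, and the research team also runs the randomisation. Both minimisation factors, department and age group, are known before consent. The physician or nurse makes the first approach and the physician checks eligibility, so the researcher's opening is limited to the call and the meeting.

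**4. How predictable might allocations be?**

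- From the article: 300 patients; factors department and age (cut-off 50).
- Assumed, because not stated: 8 departments (4 to 10 also tried), patients spread evenly over departments and age groups, two equal arms, ties broken at random, 400 simulated trials per setting. The guesser names the arm that is behind on the totals he or she can see.

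Let c be the share of patients who arrive when the totals are not tied, and p the probability of assigning the arm that is behind. A guesser who sees all relevant totals is right with probability

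c × p + (1 − c) × 0.5.

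- Margins, deterministic: c = 0.70, p = 1, giving 0.70 + 0.15 = 0.85.
- Margins, 80:20 coin: c = 0.80, p = 0.8, giving 0.64 + 0.10 = 0.74.
- Department-by-age cells, deterministic: c = 0.49, p = 1, giving 0.49 + 0.255 = 0.745.
- Cells, 80:20 coin: c = 0.60, p = 0.8, giving 0.48 + 0.20 = 0.68.

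For a guesser who sees only the department's own totals, the rate comes directly from the simulation. Correct guesses with 8 departments:

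| Balancing | Totals seen | Deterministic | 80:20 coin |
|---|---|---|---|
| On margins | All | 85% | 74% |
| On margins | Department only | 72% | 64% |
| Within cells | All | 74% | 68% |
| Within cells | Department only | 68% | 62% |

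Using 4, 6 or 10 departments moves these by about one percentage point. Simple randomisation gives 50%. The sample size calculation is not affected.

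**The case against.** The strongest reply is that this is a slip of wording. Randomisation by computer after consent is compatible with concealment, and the author may have meant that allocation is irrevocable, or that it is not blinded. On that reading the trial may be properly concealed, and only the sentence is at fault. This cannot be excluded, and it limits what can be concluded about conduct. It does not save the sentence, which would then misdescribe the trial's own protection.

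A reader might go further and infer that one researcher enrols, consents and randomises patients by deterministic minimisation, so that upcoming arms are visible. The article does not support this:

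- The first approach and the eligibility check lie with the treating team, the person taking consent is not named, and researchers are mentioned in the plural.
- The absence of a stated random element is silence in a condensed article and does not show that there is none.
- No passage says that running totals or coming allocations can be seen.

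The 85% figure needs all the unfavourable assumptions at once and should not be quoted alone.

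**Conclusion.** The statement that concealment is impossible is wrong and has to be replaced. This conclusion rests only on the article's own description of the sequence and needs no assumption.

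Whether the trial is actually exposed to selective enrolment is not settled by the article. If the sentence is literal, the design lacks its main protection at entry. If it is a slip, the design may be sound and the text is not. The illustrative predictability of about 62% to 85% depends on the unstated settings listed above and should be read as conditional. The tension with the argument against cluster randomisation is real, but it concerns a related risk and not the same one.

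**What to change.** Replace the sentence with, for example:

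> The allocation is generated in ALEA only after eligibility, consent and the completed baseline questionnaire have been registered; until then it is concealed from researcher, physician, nurse and patient, and it cannot be changed afterwards.

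In addition:

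- Keep the running minimisation totals hidden from everyone who recruits.
- If the minimisation does not already contain a random element, add one, for example 80:20. In the illustration with margins and all totals known, this lowers correct guesses from 85% to 74%. Hiding the totals is therefore needed as well.
- If patients have already been enrolled without concealment, say so plainly instead of rewording.

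The cost is one sentence, access control on the totals and possibly one setting. The downside is slightly less exact balance between arms. The sample size does not change.
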